### Process evaluation and qualitative work

A mixed-methods process evaluation will be conducted to explore how AF screening is delivered and perceived at practice and patient levels. Qualitative work will seek to understand participant experiences of being invited to, and taking part in, the study.

These will contribute to refining the theory of the intervention, which will help provide recommendations for an acceptable and sustainable screening programme at scale.

### Economic analysis

The pilot data will be used to update a published model, composed of a decision tree followed by a Markov model.^23^ The purpose of this model is to confirm that it is plausible that screening might be cost-effective using the parameters obtained in this pilot trial. All patients entering the decision tree will incur an invitation cost and the test cost will be applied to those patients who accept screening. Screen-negative patients will not accrue any additional costs and quality-adjusted life-years (QALYs). The remaining patients are true positive and, thus, will enter the Markov model. This model will simulate their survival trajectories accounting for their condition and, their lifetime costs and QALYs, which will be discounted at a 3.5% annual rate and half-cycle corrected.

The costs needed to implement the screening programme will be calculated using a microcosting approach to include all the relevant costs, such as the invitation cost and cost due to the device use (eg, shipment of the device and the training to use the device).^66^ Where needed, the costs incurred by the National Health Service (NHS) will be updated using the most recent available data, such as the British National Formulary for the cost of anticoagulant therapies.^67^

The model will be employed to perform a probabilistic analysis and compute the total costs and QALYs. The differences in costs and QALYs between the SAFER intervention and usual care will be calculated and combined to obtain the incremental cost-effectiveness ratio. Likewise, the expected value of perfect information (EVPI) will be calculated by assuming that the value of one QALY is equal to £20 000, which reflects the cost-effectiveness threshold used by the NICE. Then, the EVPI will be projected to the national level considering the eligible population for the screening and assuming that the screening programme will be provided for the next 10 years.^68^

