#### Zenicor device

The screening device being used is the Zenicor hand-held single-lead ECG device. This device is usable in any location, allows repeated ECGs, and can store and transmit multiple ECG traces to a central system for analysis.^21 24^ Photoplethysmography^56^ and blood pressure machines^57^ have not proved accurate enough, and stakeholder discussion deemed patches less practical. The diagnostic model of the Zenicor device, its associated diagnostic algorithms and subsequent cardiologist review have been used successfully at scale in the STROKESTOP AF screening trial in over 7000 participants.^42 58^ The algorithm for detecting AF showed a sensitivity of 98% and specificity of 88%.^59^ A photograph of the Zenicor device is shown in figure 2.

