#### Screening results

A proprietary algorithm will analyse the ECG traces and place a digital flag on ECGs that might show AF. These will be reviewed by a cardiologist or cardiac technician who will determine whether AF or any other important rhythm disturbance is present. If there is uncertainty, the trace will be reviewed by another cardiologist. A confirmatory 12-lead ECG is not required.^60^ The cardiologists will create a report with recommendations for the GP. Possible results are shown in table 2.

**Table 2 T2:** Categories of screening results as reported to general practices in the safer trial

Diagnosis	Definition
1. AF ≥30 s	AF is observed for a continuous period of 30 s. Sufficient readable beats (ie, disregarding poor quality sections of an ECG) show AF
2. Cannot exclude AF ≥30 s	Indeterminate result—usually due to poor quality ECG traces
3. Other significant arrhythmia	This may include, but is not limited to: Second/third degree heart block Ventricular tachycardia Supraventricular tachycardia Any other significant arrhythmia
4. No AF ≥30 s detected	This will include, but is not limited to: Sinus rhythm AF <30 s Bradycardia Ectopic beats
5. Screening failure	Unable to record any ECGs of sufficient quality for review

AF, atrial fibrillation.

The trial team will send the screening results to the practice, including copies of relevant ECG traces for positive (AF or other) diagnoses. The GP can access ECG traces and reports for all of their patients freely via the Zenicor web-based system. Practice staff will notify participants of their screening result.

For results 1–3 (table 2), the practices will offer participants a consultation to discuss the result and its appropriate management. GPs are not provided with data on burden of AF, so this will not be considered. See figure 3 for a trial schematic. Practices are monitored to ensure that all patients who are found to have AF are reviewed by their GP.

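### The economic model's two-way split has no place for indeterminate and other-arrhythmia results, although both lead to an offered GP consultation

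*Protocol article*

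**What the plan says.** All references are to the protocol article.

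- **Economic analysis, costs for everyone:** "All patients entering the decision tree will incur an invitation cost and the test cost will be applied to those patients who accept screening".
- **Economic analysis, the split:** "Screen-negative patients will not accrue any additional costs and quality-adjusted life-years (QALYs). The remaining patients are true positive", and these patients go on to the Markov model.
- **Economic analysis, costing:** "The costs needed to implement the screening programme will be calculated using a microcosting approach to include all the relevant costs". The examples given are the invitation and the use of the device.
- **Economic analysis, purpose:** "The purpose of this model is to confirm that it is plausible that screening might be cost-effective using the parameters obtained in this pilot trial". The expected value of perfect information (EVPI) is computed at £20 000 per QALY and projected nationally over 10 years.
- **Screening results, Table 2:** five results. Result 1 is AF, 2 is an indeterminate result in which AF cannot be excluded, 3 is another significant arrhythmia, 4 is no AF, and 5 is a failed screen. For results 1 to 3, "the practices will offer participants a consultation to discuss the result and its appropriate management".
- **Aim:** the economic analysis is one of the inputs to the decision to proceed to the main trial.

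**The concern.** The tree described in Economic analysis has two exits, while the screening pathway produces a third kind of participant. Someone with result 2 or 3 has not been found to have AF, but is not finished with either: a consultation is offered, and further tests may follow. If such people count as screen-negative, the rule of no additional costs contradicts the pathway. If they count as the remainder, they enter a lifetime model as true AF cases.

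Consultations triggered by these results arise only where screening is offered, and their cost cannot be negative, so leaving it out lowers the incremental cost of screening. The rule that every remaining patient is a true positive also fixes at zero a quantity that could be varied, so its uncertainty reaches neither the probabilistic analysis nor the EVPI. Both matter because the model feeds the decision to proceed.

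**Working it through.** The document states no cost-effectiveness ratio, no share of results 2 and 3 and no unit cost, so there is no figure to reproduce. The check compares the two sections and then shows how large the gap could be.

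**Mapping Table 2 to the tree**

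- Result 1: true positive, enters the Markov model.
- Result 4: screen-negative, invitation and test cost only.
- Result 5: no consultation is attached, and the test cost already applies to those who accept screening, so no extra branch is needed.
- Results 2 and 3: consultation offered, and neither exit fits.

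**Inputs from the document**

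- 12 intervention practices × 350 = 4200 consented (Sample size).
- Screened: 4200 × 0.85 = 3570 (uptake from Box 1).
- New AF: 3570 × 0.03 = 107 (yield from Box 1).
- Value of a QALY: £20 000 (Economic analysis).

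**Assumed inputs, not in the document**

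- q, share of screened people with result 2 or 3: 1% to 10%, which is 36 to 357 of 3570.
- c, cost of the consultation and work-up per such person: £40 to £250.
- g, QALY gain per newly detected AF case: 0.05 or 0.2.
- f, residual false-positive AF after cardiologist review, as a share of those screened: 0.1% to 1%.

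**If results 2 and 3 are treated as screen-negative**

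Omitted cost per screened person = q × c. Per newly detected case, divide by 0.03. The shift in the ratio = q × c / (0.03 × g).

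| q | c | Per screened person | Per new AF case | Shift, g = 0.2 | Shift, g = 0.05 |
|---|---|---|---|---|---|
| 1% | £40 | £0.40 | £13 | £67 per QALY | £267 per QALY |
| 5% | £100 | £5.00 | £167 | £833 per QALY | £3333 per QALY |
| 10% | £250 | £25.00 | £833 | £4167 per QALY | £16 667 per QALY |

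At £20 000 per QALY, £13 to £833 per case is worth 13.33/20 000 = 0.0007 to 833.33/20 000 = 0.042 QALY. The denominator counts only new AF. Gains in people with known AF who start anticoagulation after screening would make the shifts smaller.

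**If they are treated as the remainder**

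Their share of the modelled AF cohort, ignoring known AF, is q / (q + 0.03). This is 0.01/0.04 = 25% to 0.10/0.13 = 77%.

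**The true-positive rule**

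Taking the 3% as true cases, the predictive value is 0.03 / (0.03 + f). This is 0.03/0.031 = 97% at f = 0.1% and 0.03/0.04 = 75% at f = 1%. If the 3% already includes the false positives, it is (0.03 − f)/0.03, or 97% to 67%.

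**The case against.** The strongest defence has three parts.

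- **Microcosting covers it.** The costing sentence promises all relevant costs, and its examples are an open list. Consultations after results 2 and 3 could sit there. This stands in part: nothing excludes them. But the sentence concerns the cost of implementing the programme, its examples stop at invitation and device, and it does not clearly override the rule of no additional costs.
- **The article is a summary.** The tree updates a published model that is not shown, and branch detail may be in the full protocol. This would answer a mere silence. Here the article states a rule, and the rule conflicts with its own Table 2.
- **Reviewed AF is the trial's diagnostic standard.** No confirmatory 12-lead ECG is required, and the pilot describes no independent reference standard. This stands: a predictive value cannot be estimated from the pilot, so only a sensitivity analysis over assumed values is possible.

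A reader might infer more than the document supports:

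- *Screen-negatives cost nothing.* They carry the invitation and test costs. Only costs after that are excluded.
- *The model is biased in favour of screening.* The cost omission runs that way, but any health gain from acting on other arrhythmias, or from AF later confirmed after an indeterminate result, is also left out. The net direction is unproven, and for the EVPI it is unknown.
- *The 88% specificity in the Zenicor device section disproves the true-positive rule.* That figure describes the algorithm before cardiologist review, and the section does not say whether it is per trace or per person.
- *An EQ-5D comparison among people without AF would fill the gap.* Controls have no screening result, so that comparison would not be a randomised one.

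**Conclusion.** The point holds as a conflict between two sections. The tree as stated cannot place results 2 and 3, and either placement misstates something: downstream costs if they are negatives, AF status if they are the remainder. The rule that all remaining patients are true positives is a fixed assumption that the document does not test.

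The size is unknown. Under the assumed ranges the cost omission shifts the ratio by about £70 to £16 700 per QALY. The top of that range needs the highest frequency, the highest cost and the smallest QALY gain together. The stated purpose is only to show that cost-effectiveness is plausible, and a shift near the lower end would not disturb that. The pilot's own result frequencies would narrow the range considerably. The change is worth making because it is cheap and the analysis informs the decision to proceed.

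**What to change.** 1. Add a branch to the decision tree for results 2 and 3, with probabilities taken from the pilot's observed frequencies.
2. Cost the consultations and further tests that these results trigger. If they are already in the microcosting, say so and avoid counting them twice.
3. Give those frequencies and costs distributions in the probabilistic analysis, so that they reach the ratio and the EVPI.
4. State whether health effects of results 2 and 3 are modelled or held at zero.
5. Replace the fixed true-positive rule by a sensitivity analysis over an assumed residual false-positive share after cardiologist review, for example 0% to 1% of those screened.

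Possible wording: *Participants with an indeterminate result or another significant arrhythmia form a separate branch, which carries the cost of the consultation and any further tests. Its probability is taken from the pilot. The share of reported AF that is false positive is varied in sensitivity analysis.*

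The cost is modest extra modelling. The frequencies come from the screening reports that the trial already produces, while unit costs for the consultations and tests must be found. The ratio may become slightly less favourable to screening.

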### Management and oversight

The University of Cambridge and NHS Cambridgeshire & Peterborough Clinical Commissioning Group are cosponsors. The trial management group (consisting of the chief investigator and researchers from each group) and the programme steering committee (PSC), which has an independent chair and four independent members, will appraise data and decide on continuation and course of the study in consultation with the NIHR. An active risk register has been compiled in consultation with the funder and sponsors, and will be monitored and updated throughout.

### Patient and public involvement

The SAFER programme has been guided since inception by patient and public representatives who participate in all-investigator meetings. [name], chief executive and founder of the Atrial Fibrillation Association (AFA), has been involved in the development of the research from the outset as a patient and public involvement (PPI) member. The AFA represents over 64 000 people with AF.

Additional PPI members have been recruited independently of the AFA. Many are in the age range for AF screening; some of them either have AF or have a partner with AF. The PSC has an independent lay member who is a stroke survivor.

The PPI members are consulted throughout the trial on all aspects of the research, including: possible psychological harms of screening; participant-facing documents; how to approach participants; instructing participants on trials and screening procedures; web-based materials and qualitative data-collection material. The AFA will help with dissemination of the findings through its website and members.

## Ethics and dissemination

### Ethics

#### Ethical approval

The SAFER pilot trial has received a favourable ethical opinion from the London—Central NHS Research Ethics Committee (19/LO/1597) and the Confidentiality Advisory Group (19/CAG/0226). Modifications of the full protocol are detailed in amendments. Important modifications will be communicated to the sponsors, funder, collaborators, practices, participants, trial registries and disseminators as relevant.

#### Consent

Participants will be required to provide valid written informed consent, either via post or online. Consented participants from screening practices will be approached with an offer of AF screening.

### Dissemination

The study will generate peer-reviewed publications to disseminate to academics, health professionals, policy-makers, patient organisations and the print and electronic media. After publication, data may be available to others according to data sharing agreements in compliance with the funder and sponsor policies. Summary documents will be made available to participants at the end of the study. PPI groups and media engagement will help disseminate findings. Accessible reports will be generated for national screening committees, commissioners and other decision-makers. Funders’ reports will be submitted in accordance with their policies.
